**Inclusion Criteria**
• 18–26 years of age
• Being strangled during sex, on average, three times in the past month (strangulation group)
• Age-matched participants with no lifetime experience of being strangled during sex (control group).

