## Abstract

Sexual strangulation (also referred to as choking during sex) has become increasingly prevalent among young adults and disproportionately affects females. Epidemiological studies indicate that more than half of college-aged women report a lifetime history of being strangled during sex, and it is most often described as consensual. Despite its widespread occurrence, little is known about the acute and cumulative neurological consequences of this behavior. Pilot studies suggest associations between frequent sexual strangulation and elevations in blood biomarkers of neural injury, alterations in brain structure and connectivity, and increased mental health symptoms; however, existing evidence is limited by cross-sectional designs, short-term follow-ups, and small sample sizes. This prospective cohort study is designed to characterize both the acute and longitudinal neurological effects of sexual strangulation using multimodal assessments. A total of 200 young adult females (100 with frequent sexual strangulation exposure and 100 controls with no lifetime strangulation history), along with a pilot cohort of 40 males, will undergo comprehensive evaluations including blood-based biomarkers of neural injury and inflammation, multimodal MRI, cognitive and oculomotor testing, retinal imaging, and mental health assessments. Acute neurological responses will be assessed approximately 24 hours following a sexual event involving strangulation (or non-strangulation sex in controls), while longitudinal follow-up will occur every six months over 30 months to examine cumulative exposure effects. Semi-structured interviews conducted at each time point will characterize strangulation practices, contextual factors, consent dynamics, and associated symptoms. The primary objectives are to (1) examine baseline group differences in neurological health between individuals with frequent sexual strangulation exposure and non-strangulation controls, (2) identify acute neurological alterations following sexual strangulation, (3) determine associations between cumulative strangulation exposure and neural cellular, physiological, and functional integrity over time, and (4) characterize young adults’ experiences, contextual factors, and perceptions of sexual strangulation through semi-structured interviews. Collectively, this study aims to establish temporal relationships between sexual strangulation and neurological health outcomes and to inform clinical guidance, sexual health education, and harm-reduction strategies related to this increasingly common sexual practice.

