Emerging pilot data suggest that sexual strangulation may be associated with both short-term and longer-term neurological alterations. Specifically, young adult females who have been strangled at least 4 times during sex in the past month showed higher levels of circulating S100B level [26], which is indicative of astroglial activation, increased cortical thickness in widespread brain regions [27], interhemispheric differences in neural activation patterns [28], and inefficient neural effort during working memory tasks compared to strangulation naïve controls [29]. Furthermore, a single event of being strangled during sex was also associated with acute impairments in ocular convergence, blunted positive effects of sexual activities on mental health [30], and elevations in several inflammatory cytokines and chemokines (e.g., CCL-2, VEGF-A) [31]. However, interpretation of these findings has been constrained by methodological limitations, including reliance on a cross-sectional design, smaller sample sizes, and limited ability to distinguish pre-existing differences from strangulation-related effects.

A critical gap is the absence of longitudinal, multimodal studies capable of characterizing neurological health at baseline, assessing acute responses following sexual strangulation, and tracking cumulative effects over time. Without such data, it remains unclear whether observed neurological differences reflect pre-existing vulnerabilities, transient brain responses, or progressive neural changes associated with repeated exposure. Additionally, little is known about how contextual variables, such as frequency, methods, perceived consent, and subjective experiences, may modify neurological outcomes.

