## Methods

### Participants

This prospective cohort study will enroll a total of 240 young adults, including 200 females and a pilot cohort of 40 males. Female participants will be assigned to one of two primary groups: individuals with frequent exposure (≥4 times per month) to sexual strangulation (n = 100) and age-matched controls with no lifetime history of being strangled during sex (n = 100). An additional pilot cohort of males (n = 20 per group) will be recruited to generate preliminary data on neurological correlates of sexual strangulation in males. The recruitment is anticipated to start in late February 2026 until March 2029, and all data collection is expected to finish by May 2030. Primary analyses will finish by May 2031. Eligible participants will be between 18 and 26 years of age and recruited primarily from the Indiana University campuses and surrounding community. Longitudinal follow-up of enrolled participants will extend up to 30 months. All participants will provide electronic written informed consent prior to enrollment. The initial study protocol has been approved by the Indiana University Institutional Review Board (#27400) on Jun 04, 2025. Upon completion of primary and secondary analyses, all relevant data will be made publicly available in sites including *brainlife* and inter-university Consortium for Political and Social Research (ICPSR).

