Inclusion and exclusion criteria are summarized in Table 2. For the strangulation group, inclusion requires self-report of being strangled during sex at least four times in the month prior to enrollment, which will be verified during a screening interview. Control participants must report no lifetime history of sexual strangulation. Exclusion criteria are limited to conditions necessary for participant safety or study feasibility and include head or neck injury in the past 6 months including concussions, current diagnosis of psychosis, schizophrenia, and seizure disorder, currently taking anti-psychotic medicine, history of brain aneurysm or brain tumor, and current pregnancy. Common psychiatric conditions prevalent in young adults, including depression, anxiety disorders, bipolar disorder, and attention-deficit/hyperactivity disorder (ADHD), will not be excluded and will be assessed and accounted for analytically. Additionally, participants with implanted metal/electro/magnetic devices will not undergo MRI data collection, but they will complete all other assessments; thus, not excluded from the study.

**Table 2 pone.0344672.t002:** Inclusion and exclusion criteria.

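### The entry threshold for the strangulation group is contradictory: Table 2 says an average of three events in the past month, the Methods text says at least four

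*Protocol article*

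**What the plan says.** The protocol article states the exposure definition for the strangulation group in four places.

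- Table 2 (Inclusion Criteria): "Being strangled during sex, on average, three times in the past month (strangulation group".
- Methods, Participants, first paragraph: "individuals with frequent exposure (≥4 times per month) to sexual strangulation (n = 100".
- Methods, Participants, second paragraph: "inclusion requires self-report of being strangled during sex at least four times in the month prior to enrollment". The same paragraph presents Table 2 as a summary of the criteria and says that the self-report will be verified in a screening interview.
- Introduction, on the pilot findings: "young adult females who have been strangled at least 4 times during sex in the past month".

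For controls, Table 2 requires "no lifetime experience of being strangled during sex (control group". Both paragraphs of the Participants section say the same in substance. The Abstract uses a shorter phrase, "100 controls with no lifetime strangulation history".

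**The concern.** Nobody is randomised in this study, so the entry rule is the exposure definition. Group is the primary independent variable in the baseline models, and the group-by-time interaction is the main contrast in the acute and longitudinal models. The rule that sets who counts as frequently exposed appears with two different values.

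Two things are at stake. First, staff applying the table and staff applying the text would reach different decisions about the same woman, so the composition of the exposed group could depend on which statement was followed. Second, the pilot findings that motivate the study come from women with at least four events in the past month, and the Sample size section draws partly on pilot data. Admitting women below that level would move the cohort some way from the population in which those effects were seen, and could weaken the contrast with controls.

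**Working it through.** No arithmetic in the plan bears on this point, so the check sets the statements side by side and applies each to a woman with a given number of events in the month before enrolment.

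| Events in past month | Participants section (four or more) | Table 2 read as a minimum of three | Table 2 read literally as three |
|---|---|---|---|
| 2 | not eligible | not eligible | not eligible |
| 3 | not eligible | **eligible** | **eligible** |
| 4 | eligible | eligible | unclear |
| 5 | eligible | eligible | unclear |

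1. **The conflict.** At exactly three events, both readings of Table 2 admit the woman and both paragraphs of the Participants section refuse her. No reading makes the two agree.

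2. **Table 2 on its own terms.** It has no *at least*, so read literally it does not say what happens to a woman with four or five events. It also combines *on average* with a single past month, and one month gives one count with nothing to average over. If an average over several months was meant, that is a different reference period. For example, monthly counts of 2, 3 and 4 average (2 + 3 + 4) / 3 = 3, while the most recent month alone gives 4.

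3. **Which statement is the outlier.** Both paragraphs of the Participants section and the pilot definition in the Introduction use four. Only Table 2 uses three. Because the text calls Table 2 a summary of the same criteria, a separate, looser rule was evidently not intended.

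4. **Size.** The floor differs by 4 − 3 = 1 event, or 1/4 = 25% of the higher floor. Turning that into a loss of contrast needs two quantities: the share of the exposed group that would enter with exactly three events, and the size of their effect relative to women with four or more. The documents give neither, so no dilution figure can be derived.

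**The case against.** The best counter-argument is that this is a drafting slip in a summary table. The operative text is firm (inclusion *requires* at least four) and says that this count is verified at interview. The prescreening questionnaire is not shown and may already carry the right number. Even if some women with three events entered, the longitudinal plan models strangulation frequency as a time-varying predictor within the exposed group, so their data would still be informative there. A slip is indeed the likeliest explanation. It does not remove the point, because Table 2 is the formal list of inclusion criteria and nothing in the article says which statement prevails.

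Several stronger readings are tempting but not supported.

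- *Every participant's group depends on the threshold.* It does not. Controls have no lifetime sexual strangulation under either rule. A woman with three events is either in the exposed group or out of the study, and never becomes a control. Only women near the threshold are affected.
- *Screeners will work from Table 2.* The article does not say so.
- *The pilot effect sizes no longer apply.* This goes too far. The Sample size section also cites related literature, and its longitudinal d = 0.50 lies below the lowest pilot value it lists (0.52).
- *The control definition conflicts as well.* Both Participants paragraphs and Table 2 agree on no lifetime strangulation during sex. Only the Abstract is shorter, and its phrase follows a mention of sexual strangulation exposure in the same clause, so it reads as shorthand. Requiring controls to be free of strangulation of any kind would be a different design preference. Any dilution figure for controls with non-sexual strangulation would rest on an assumed share and an assumed equal effect, and would say nothing about three versus four.

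**Conclusion.** The point holds for the exposed-group threshold. Table 2 contradicts both statements in the Participants section and departs from the pilot definition, and its wording cannot be applied as it stands. This follows from the text alone and rests on no numerical assumption. It matters because the rule defines the exposed group in every main between-group analysis.

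Its practical size is unknown: the eligibility of women with exactly three events is in doubt, and the documents do not say how many there are. The finding does not show that the stated power is wrong, that anyone has been misclassified, or that the control group is badly defined. The Abstract's wording on controls is at most a minor edit.

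**What to change.** State one threshold, with an explicit *at least* and one reference period, in both paragraphs of the Participants section, in Table 2 and on the prescreening form. Since Table 2 is the outlier, the natural correction is to change its line to at least four events in the month before enrolment and to drop *on average*. If three was intended, change both Participants statements instead and justify the departure from the pilot definition.

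Recruitment was anticipated from late February 2026, so screening may have begun. In that case the sponsor should confirm which rule was applied, check enrolled participants against the agreed rule, and record any who meet only the looser one.

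As an optional tidy-up, the Abstract can describe controls as having no lifetime history of *sexual* strangulation.

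The cost is a one-line edit to Table 2, a check of the prescreening form and, under the four-event rule, a slightly smaller eligible pool than Table 2 would allow. No new data collection or change to the analysis is needed.

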**Exclusion Criteria**
• Currently pregnant
• Have had a head or neck injury within the past 6 months
• Current diagnosis of psychosis, schizophrenia, and seizure disorders
• Currently taking anti-psychotic medicine
• History of brain aneurysm or brain tumor

Participants may be withdrawn from the study without their consent if they become ineligible during the study period, exhibit intoxication at study visits, or engage in behavior that compromises participant or staff safety. Participants who change sexual behavior during the study (e.g., controls who begin engaging in sexual strangulation or strangulation participants who discontinue the behavior) will continue follow-up when feasible, with data contributing to primary analyses up to the point of behavioral change and exploratory analyses thereafter. Table 3 indicates the status of enrollment and Fig 1 depicts the study flow.

**Table 3 pone.0344672.t003:** SPIRIT checklist, February 2026.

	STUDY PERIOD						
	Enrolment	Allocation	Post-allocation				Close-out
**TIME POINT**	** *-t* ** _ ** *1* ** _	**0**	** *t* ** _ ** *1* ** _	** *t* ** _ ** *2* ** _	** *t* ** _ ** *3* ** _	** *t* ** _ ** *4* ** _	** *t* ** _ ** *x* ** _
**ENROLLMENT:**	0						
**Eligibility screen**	0						
**Informed consent**	0						
**Allocation**		0					
**ASSESSMENTS:**							
** *[Demographics, Questionnaire, SCID-5, interview]* **		0					

**Fig 1 pone.0344672.g001:**
[figure not shown]
Schematic study design.

### Study procedures

#### Study design overview.

This study employs a mixed-methods prospective cohort design integrating multimodal neurological assessments and semi-structured interviews (Fig 1). Participants will be enrolled into either a sexual strangulation group or a non-strangulation control group based on screening criteria and will undergo baseline neurological and behavioral assessments. Acute neurological responses will be evaluated following a sexual event involving strangulation (or non-strangulation sex in controls), and longitudinal follow-up assessments will be conducted every six months for up to 30 months to characterize cumulative exposure effects and temporal changes in neurological health.

#### Screening and enrollment.

Potential participants will be identified primarily through a campus-wide probability survey focused on sexual health and behavior that is administered during the first two to three years of the study, supplemented by community-based recruitment strategies, including university’s classified sites and social media platforms. Individuals who indicate willingness to be contacted for follow-up research will be randomly stratified (via Randomization function within *R*), with first- and second-year students taking the priority spots to accommodate those who are likely be in school throughout the entirety of 30 months follow-up. Invited participants will complete a prescreening questionnaire to confirm eligibility criteria, including age, sexual strangulation history, and key exclusionary medical or neurological conditions. Eligible individuals will be invited to a virtual consent meeting, during which electronic written consent will be obtained. Following the virtual consent meeting, participants will undergo an additional virtual meeting, and research staff will administer QuickSCID-5 (Quick Structured Clinical Interview for DSM-5 Disorders) to assess current and history of mental health diagnosis. When participants endorse any symptoms related to psychosis and/or schizophrenia, research staff will then conduct a SCID-5 Research Version – Psychotic module B/C to determine the eligibility of participants [32]. During the virtual meeting, research staff will also administer The Alcohol, Smoking and Substance Involvement Screening Test (ASSIST) [33]. When participants meet the inclusion criteria and are free of exclusionary criteria, they will be enrolled in the study and assigned a study-specific ID. Prior to baseline visit, participants are asked to abstain from the following behaviors and caffeine: abstain from sex involving choking and any activities involving pressing or squeezing of the neck (e.g., martial arts chokeholds) 48 hours prior to lab visit, no strenuous exercise (e.g., sports games, cross-fit) 24 hours prior to the visits, no mild to moderate exercise on the day of lab visit, no sexual activities on the day of lab visit, and no caffeine on the day of lab visit.

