### Specific aims

Aim 1 To examine potential group differences at baseline in neurological health between the strangulation and control groups through comprehensive neurological measures.Hypotheses: (1a) Significant differences in brain activation patterns and neuronal connectivity, increases in blood biomarkers for astrogliosis, inflammation, and axonal microstructural injury, alteration in retinal integrity, and declines in cognitive, ocular-motor, and mental health function will be observed in the strangulation group compared to controls. (1b) We will explore potential mediating factors, including behavioral, history, and broader demographic factors, driving group differences in neurological health.Aim 2: To identify the acute neurological effects of sexual strangulation through the response profile of multimodal neuroimaging, blood biomarkers, cognitive and mental health assessments, and visual health assessments.Hypotheses: (2a) Within the strangulation group, significant alterations in brain activation patterns and neuronal connectivity, increases in blood biomarkers for astrogliosis, inflammation, and axonal microstructural injury, alteration in retinal integrity, and declines in cognitive, ocular-motor, and mental health function will be observed acutely (~24h) after being strangled during sex compared with baseline. (2b) The control group will have no worsening of neurological outcomes, resulting in a significant group difference at a post-acute time point. Also, individual cerebral hemodynamics via perfusion measure and fMRI activation patterns in risk and reward pathways will be explored in response to acute sexual strangulation events.Aim 3 To determine the associations between cumulative exposure to sexual strangulation and neural cellular, physiological, and functional integrities.Hypotheses: (3a) Frequent sexual strangulation will correlate with negative neurological outcomes, and this association will strengthen over time. (3b) The neurological impact of cumulative strangulation will be pronounced in blood biomarkers, indicative of astrogliosis, inflammation, and reduced axonal microstructural integrity, surface and subcortical morphology, neural activation patterns in the limbic regions, and cognitive function. (3c) Cumulative effects of sexual strangulation will also be captured through a series of mental health and visual health assessments. For those switching their sexual behavior (e.g., controls who report new onset of strangulation experiences), an exploration of how brain health changes as they initiate or cease engaging in sexual strangulation will be conducted.Aim 4: To examine longitudinal characteristics, perceptions, and experiences of sexual strangulation via semi-structured interviews.Semi-structured interviews in connection with each laboratory visit will address how one’s experiences with sexual strangulation change over time in terms of frequency, duration, methods of strangulation, consenting status, motivations, and associated symptoms. These data will not only play a crucial role in informing behavioral targets for educational guidelines and interventions, but also identify behavioral patterns and contextual factors that modify neurological outcomes. For example, our exploratory analysis will examine the role of alteration in consciousness (AIC), such as visual changes, disorientation, loss of consciousness, or dizziness) on neurological outcomes by comparing AIC and non-AIC subgroups.Exploratory Aim 5: To examine neurological implications of sexual strangulation among a pilot cohort of males.Since no neurological data related to sexual strangulation exist for males, pilot cohorts of males (n=20 per group) will be included to generate preliminary data and hypotheses for future research.Exploratory Aim 6: To explore various contextual and modulatory factors that are influencing neurological and psychological wellbeing over time in relation to sexual strangulation and non-strangulation related sex.Leveraging comprehensive assessments of participants’ demographics, prior sexual history, and contextual factors (e.g., menstrual cycle, birth control, sleep, substance/tobacco/alcohol use), we will explore how these factors contribute to individual responses to sexual strangulation and general sexual activities. This aim will include exploration of those who switch sexual behavior (e.g., stopping strangulation or control starting to engage in strangulation).

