#### Acute assessment following sexual activity.

Participants eligible for the acute aim will be monitored following baseline assessment using brief daily electronic surveys to determine the occurrence of sexual activity and the presence or absence of strangulation. For participants in the strangulation group, an acute laboratory visit will be scheduled within approximately 24 hours following a sexual event involving strangulation. For control participants, an acute visit will be scheduled within approximately 24 hours following a sexual event without strangulation. Participants who do not engage in sexual activity during the monitoring period will remain eligible for longitudinal follow-up but may not contribute to acute analyses. The acute visit will replicate key components of the baseline assessment, including blood collection, neuroimaging, cognitive testing, oculomotor and retinal assessments, and mental health questionnaires. These data will be used to characterize short-term neurological responses associated with sexual strangulation relative to baseline and control conditions.

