#### Acute effects.

To examine the acute neurological effects of sexual strangulation, we will use a series of generalized linear mixed models (GLMMs) (or linear mixed-effects models for normally distributed outcomes) with each neurological variable as the dependent variable and visit type (baseline vs. post-acute) as the primary within-person predictor. Models will include a participant-specific random intercept to account for repeated measures. The primary interest will be the group (strangulation vs. control) × time (baseline vs. post-acute) interaction. Within-group time-effects will also be examined to assess group-specific time trends. Prespecified covariates will consider age, prior concussion history, and mental health diagnosis and/or mental health symptoms, as well as potentially adjusting for time since the most recent sexual event. We will also explore by including menstrual cycle phase and/or ovarian hormone levels as covariates. For neuroimaging outcomes, standard acquisition/quality covariates (e.g., motion indices) will be included. To address multiple comparisons across numerous endpoints, FDR will be applied within modality (biomarkers, imaging, ocular/retinal, cognition/mental health).

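### A 48-hour minimum washout in women strangled about weekly can leave residual marker at baseline, shrinking the acute change for slow-clearing markers by an amount the acute model does not handle

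*Protocol article*

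**What the plan says.** All places are in the protocol article.

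- **Washout (Screening and enrollment).** Participants are asked to "abstain from sex involving choking and any activities involving pressing or squeezing of the neck" for 48 hours before the laboratory visit. Other sexual activity is barred only on the day of the visit.
- **Exposure (Participants).** The strangulation group is defined as "individuals with frequent exposure (≥4 times per month) to sexual strangulation", and inclusion requires "self-report of being strangled during sex at least four times in the month prior to enrollment". The inclusion list in Table 2 gives an average of three times in the past month instead; the two need reconciling.
- **Acute visit (Acute assessment following sexual activity).** For this group, "an acute laboratory visit will be scheduled within approximately 24 hours following a sexual event involving strangulation".
- **Hypothesis (Specific aims, 2a).** Changes "will be observed acutely (~24h) after being strangled during sex compared with baseline".
- **Model (Statistical analyses, Acute effects).** A mixed model takes "visit type (baseline vs. post-acute) as the primary within-person predictor", with a participant random intercept. The group × time interaction is of primary interest. How long ago the most recent sexual event took place is listed as a possible adjustment only.
- **Controls (Participants).** No lifetime history of being strangled during sex.

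**The concern.** Acute minus baseline equals the new event's effect at 24 hours less the decay, between the two visits, of whatever earlier events had left behind. If a marker clears within a day or two, little is left at baseline and the contrast is nearly clean. If it clears over several days or more, part of the event's effect is subtracted. How much depends on the days between the last strangulation and baseline, which differ between women.

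The protocol's own hypotheses make this relevant. Hypothesis 1a expects astroglial, inflammatory and axonal markers to be raised already at baseline in this group; hypothesis 2a expects the same classes to rise from that baseline. Any part of the first that is residue from recent events reduces the second. The group × time term does not help, because controls have no such residue.

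The optional covariate runs on the wrong clock. A woman could have been strangled three days before baseline and had other sex one day before, and the covariate would read one day. At the acute visit it is about one day for nearly everyone by design, so it partly duplicates the visit term. Entered as a main effect, it also does not let the visit effect vary with washout.

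At stake is the reading of hypothesis 2a for slow markers: a weak or null change could reflect a short washout and not a weak response.

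**Working it through.** **Plan's own figure.** The Sample size section gives 60 females per group, d = 0.60, alpha 0.01 and 80% power for the acute aim. Sidedness and within-person correlation are not stated. Two-sided, with d on the SD of the change score, power = Φ(0.60·√(60/2) − 2.576) = Φ(0.711) = 76.1%, and 80% needs 65 per group. One-sided, power is 83.1%. With d on the raw SD and a within-person correlation of 0.54, 60 per group gives 80.2%. The figure can be neither confirmed nor refuted. It affects only what carry-over costs in power, not whether carry-over exists.

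**Inputs from the article.** Washout of at least 48 h; acute visit at 24 h; four events per 30 days, so a mean gap D = 30/4 = 7.5 days.

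**Assumptions.** Half-life h (none is given), an immediate rise, exponential decay, equal increments and steady state.

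**Formula.** Let baseline fall u days after the last event. Each level is a sum over past events, with factor S = 1/(1 − 2^(−D/h)).
- Acute level: S·2^(−1/h)
- Baseline level: S·2^(−u/h)
- True single-event effect at 24 h: 2^(−1/h)
- Retained share: R = [1 − 2^(−(u−1)/h)] / [1 − 2^(−D/h)]

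Example, u = 2 and h = 2: (1 − 0.707)/(1 − 0.074) = 0.293/0.926 = 0.32.

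| Half-life | u = 2 days (floor) | Mean over u from 2 to 7.5 days | u = 7 days |
|---|---|---|---|
| 1 day | 50% | 88% | 99% |
| 2 days | 32% | 74% | 94–95% |
| 7 days | 18% | 58% | 85–86% |
| 30 days | 14% | 52% | 81% |

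With D = 7 the 7-day half-life at the floor gives 19%. With Table 2's three events a month (D = 10, baselines from 2 to 10 days), half-lives of 1, 2 and 7 days give 50%, 30% and 15% at the floor and 91%, 79% and 60% on average, so the frequency discrepancy does not change the picture.

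**Random spacing.** Take Poisson events at λ = 4/30 per day, none in the 2 days before baseline, and the first later event as index. With k = ln2/h, expected residue at baseline is B = λ·e^(−2k)/k, and R = 1 − B·e^(k)·[1 − e^(−k)·λ/(λ+k)]. This gives 91% (1 day), 78% (2 days), 52% (5 days), 41% (7 days), 22% (14 days) and 6% (30 days). At 90 days it is slightly negative, −6%.

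**Where baselines would fall.** Regular spacing: u runs evenly from 2 to 7.5, mean 4.75 days, and 1/5.5 = 18% lie within 3 days. Random spacing: mean 2 + 7.5 = 9.5 days, median 2 + 7.5·ln2 = 7.2 days, and 1 − e^(−λ) = 12% lie within 3 days.

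**Power for group × time** at n = 60, two-sided, taking 0.60 as the full 24-hour effect (76% without carry-over), for a 7-day half-life:
- Floor: Φ(0.60·0.180·√30 − 2.576) = 2%
- Average retained share: Φ(0.60·0.575·√30 − 2.576) = 25%
- u = 7 days: Φ(0.60·0.855·√30 − 2.576) = 59%

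**The case against.** **48 hours is a floor.** Nothing in the article says that baseline is taken 48 hours after the last event. A reader might infer that the acute contrast is 24 hours against 48 hours. That is the extreme case; the typical interval under the schedules above is about 5 to 9 days. This objection stands.

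**A loss of most of the effect is not shown.** Under regular spacing more than half is retained on average at every half-life tried. Most is lost only near the floor with half-lives above about 1 day, or under random spacing with half-lives above about 5 days. Half-lives are assumed, a delayed peak would change the figures, and fast markers are barely touched. This also stands.

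**The estimand may be the increment over the usual state.** The acute section does not call baseline an unexposed reference, and hypothesis 2a can be read as change from a frequently exposed woman's habitual level. That is fair. Yet even on that reading the contrast varies with where baseline falls between events, and the plan does not fix this.

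**There is a provision for timing, and the data may exist.** The optional covariate, the testing-day questionnaires and the interviews all touch on timing or frequency, and an article need not list every item. So one cannot say that the date is not collected. But the covariate named is optional, counts any sex and is not a modifier of the visit effect.

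**The bias is mainly toward zero.** It does not manufacture an acute effect, and no section says that a null would be read as no response. True, which is why the remedy is a sensitivity analysis and a statement on interpretation.

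**Conclusion.** The concern holds in this form: a 48-hour minimum washout, in women strangled about weekly, can leave residual marker at baseline. For slow-clearing markers this shrinks the acute change and the group × time interaction, through the strangulation group only, and the covariate offered does not deal with it.

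For half-lives of 1, 2 and 7 days, the retained share is about 50%, 32% and 18–19% at the 48-hour floor and about 88%, 74% and 58% averaged over baselines 2 to 7.5 days after the last event. Random spacing lowers it for longer half-lives, to 41% at 7 days and 6% at 30 days.

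These sizes rest on assumed half-lives, an immediate peak, equal increments and steady state. The power figures also take d = 0.60 as the full 24-hour effect; if the pilot estimates already contained carry-over, the loss would be partly counted. The documents do not support the stronger claim that the acute contrast in general misses most of the event's effect.

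**What to change.** 1. Record the date of the last strangulation before the baseline visit, as one item on the testing-day questionnaire if it is not already there. It is best settled before baselines accrue, since recall is hard to recover later.
2. In place of the optional covariate, prespecify a sensitivity analysis of the acute model within the strangulation group with a visit × days-since-last-strangulation-at-baseline term, accounting for habitual frequency (for example, frequency and its interaction with visit). Report the estimated acute effect at a longer washout, such as 7 days, beside the average.
3. State that a null for a slow-clearing marker after a short washout is not evidence of no acute response.

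The abstinence instruction and visit schedule stay as they are. The cost is one item and a few model terms. The washout-specific estimate will have a wider interval, since the acute aim is powered on about 60 exposed women. Washout is also partly tied to exposure frequency: women strangled more often than weekly will rarely have a 7-day interval, so for them the estimate leans on the model. For very long half-lives the term reduces the problem but does not remove it.
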